***Outcome variables - postnatal growth***			
Attaining birth weight	Number of days	Mean/Median	After attaining birth weight after normal initial weight loss postpartum
Body weight	Kilograms	Mean/Median	1. Once every week during study intervention 2. 40 weeks of gestational age 3. 3 months of corrected age 4. 12 months of corrected age 5. 2.5 years of corrected age 6. 5.5 years of age
Body length	Centimeters	Mean/Median	1. Once every week during study intervention 2. 40 weeks of gestational age 3. 3 months of corrected age 4. 12 months of corrected age 5. 2.5 years of corrected age 6. 5.5 years of age
Head circumference	Centimeters	Mean/Median	1. Once every week during study intervention 2. 40 weeks of gestational age 3. 3 months of corrected age 4. 12 months of corrected age 5. 2.5 years of corrected age 6. 5.5 years of age
Growth chart *Z*-score	Reference Niklasson [73] and Fenton [74]	Standard deviation	1. Once every week during study intervention 2. 40 weeks of gestational age 3. 3 months of corrected age 4. 12 months of corrected age 5. 2.5 years of corrected age 6. 5.5 years of age
Body composition	Fat mass, fat-free mass (%)	Average	3 months corrected age
***Characteristics/covariates***			
Use of medical steroids	Period of treatment	Mean/Median	From birth until 5.5 years of age
Use of tetracyclines	Period of treatment	Mean/Median	From birth until 5.5 years of age
Type of enteral nutrition mothers’ own milk, donated breastmilk, formula	Percentages (%)	Proportion	During study intervention (until 34 weeks of gestational age)
Breastmilk fortification	Type	Proportion	During study intervention (until 34 weeks of gestational age)
Breastfeeding at discharge	Full, partly, none	Proportion	Discharge from neonatal intensive care unit/homecare

Daily nutritional assessment of enteral and parenteral nutrition during the intervention period will be documented in Nutrium. These assessments include all macro- and micronutrient intake including type, amount, and strategy of enteral and parenteral feeds. Data on breastmilk fortification and interruptions of enteral feeds will also be documented and collected from Nutrium.

Assessment of body composition will be made at 3 months corrected age using air displacement plethysmography (PeaPod). This is considered “the gold standard” for measuring body composition, including fat, fat-free mass, and bone density, for infants weighing below 8 kg [72]. It applies whole-body plethysmography which is a fast, reliable, and non-invasive assessment. Assessment of body composition will be documented and retrieved from patient records.

### Plans to promote participant retention and complete follow-up {18b}

Hospital discharge before 34 weeks of gestational age is very uncommon among extremely preterm infants. Therefore, the intervention will be completed during hospital admission and the drop-out rate is expected to be none or minimal. Legal guardians will be given robust information about the study both before inclusion and following enrollment, which is expected to promote study retention.

Patients will be included at a university hospital that cares for extremely preterm infants from birth, but may be relocated to satellite hospitals during the intervention. In the event of relocation, the initial university hospital and the main study coordinator are responsible for giving the cooperating satellite hospital adequate information about the study. The receiving satellite hospital will receive standardized written information, including general information about the study, how to prepare and administer the study product, and information about stool sampling. The PI for each university hospital is responsible for completing the CRF and other administrative data collection in REDCap.

Stool sampling at 12 months corrected age will be taken by the legal guardians at home if infants are not followed up at a university hospital. Instructions for legal guardians will be sent out by the neonatal follow-up clinic when informing parents about routine hospital appointments. Neonatal follow-up clinics will be given sufficient information about stool sampling before the first included infant reaches 12 months corrected age.

### Data management {19}

Data will be collected and maintained with the electronic data capture application, REDCap. REDCap is a secure web platform for building and managing online databases and surveys. Data will be accessible for all research group members but not to unauthorized personnel. Members of the research team at every site will only have access to data from their own hospital. The PI and other members from the main research group at Karolinska will have access to data collected at all hospitals. All researchers will be blinded during the study and analyses.

REDCap will be accessible to all university hospitals taking part in the research project. The software enables very robust traceability of the research output, including an audit trail that traces data entry and editing. Access to what data can be viewed and modified can be customized for each person within the research project. The data is stored automatically at two different servers around Stockholm which are backed up every hour. Data will be analyzed using the statistical analysis software, STATA.

### Confidentiality {27}

Patients will be pseudonymized and obtain a Study-ID upon inclusion. A patient identification log will be available in REDCap. Only core researchers with will have access to the identification log, and their access will be limited to that of their own university hospital. The PI and other members from the main research group at Karolinska will have access to all patient identification logs. The patient identification log will only have information about if the patient has been allocated to group C or D, so this information will still be blinded.

Management of data will be done according to the European Union’s General Data Protection Regulation (GDPR) guidelines. No unauthorized person will have access to personal data and those with access will be bound by professional secrecy. Region Stockholm is responsible for the participants’ personal data.

Legal guardians have the right to access the personal information handled in the study and correct errors if necessary. They can also request the deletion and restriction of personal data; however, this right does not apply when the data is necessary for the research in question. Legal guardians who are not content with how personal data is processed can submit a complaint to Swedish Authority for Privacy Protection.

The analysis and publishing of the results will be performed at a group level, meaning that no individuals can be traced to their data. To ensure the safety and integrity of the patients and quality of collected data, the study will be conducted in accordance with the study protocol, ICH-GCP E6 (R2) and the Declaration of Helsinki. The trial is designed in accordance with recommendations for interventional trials [68] and Consolidated Standards for Reporting of Trials (CONSORT) guidelines.

### Plans for collection, laboratory evaluation, and storage of biological specimens for genetic or molecular analysis in this trial/future use {33}

For the complete cohort, stool samples to identify possible differences in microbiome composition will be collected at the following timepoints:Directly after inclusion or at the timepoint when infant first produces stool14 ± 2 days gestational age34 weeks ± 2 days gestational age12 months corrected age ± 2 weeks

The stool samples will be collected by a nurse and stored immediately in −20°C and/or −80°C. They should be transferred frozen to a −80°C freezer at the hospital if available or at the regional biobank as soon as possible. All collected stool samples will be moved and registered at KI Biobank at Karolinska Institutet in Solna, Sweden, and handled in accordance with current biobank regulations at the end of the trial. A multicenter agreement between all biobanks included in the PEPS trial has been established. All samples will be coded with the participants’ study-ID and stored securely and separately to prevent unauthorized access and hold pseudonymization until the results have been finalized. Stool management, microbiological sampling, and complete sequencing will be done in collaboration with the Centre for Translational Microbiome Research at KI.

## Statistical methods

### Statistical methods for primary and secondary outcomes {20a}

Data will be analyzed as both per protocol and intention to treat (ITT). The primary analysis will be analyzed and reported as ITT.

#### Primary aim 1 and secondary aims 1–3

In the initial analysis, we will compare baseline characteristics of the study population between allocation groups to ensure that balance was achieved by the randomization. We will report the mean (standard deviation [SD]) or median (first quartile, third quartile) for continuous variables, and count and percentages for categorical variables. The primary analyses will be based on the ITT population including all subjects that were randomized in the study. A crude and a multivariable-adjusted standardized logistic regression will be used to calculate the relative risk (RR) and 95% CI to estimate the effect of probiotic supplementation on the risk of NEC and/or mortality (primary aim) as well as NEC, total mortality, and LOS separately (secondary aims 1–3). The randomization will be stratified per site. Thus, the analysis will adjust for this variable before standardization. A per-protocol analysis accounting for non-compliance will also be performed. All data analyses will be performed using the STATA and R software. A two-sided *p*-value of 0.05 will be considered significant evidence of the effect of the intervention.

#### Secondary aims 4 and 5

The effect of probiotic supplementation on the rate of prescription and duration of antibiotic use during hospital stay (secondary aim 4) and duration of hospital stay (secondary aim 5) will be analyzed using standardized logistic regression and linear regression model.

#### Secondary aim 6

The effect of probiotic supplementation on gut microbiome will be investigated by comparing the alpha and beta diversity of the microbiota samples. Alpha diversity measures the mean diversity within a sample while beta diversity involves a comparison of diversities between samples and will be displayed as a principal coordinate or component analysis plot.

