#### Secondary aims

To determine whether probiotic supplementation will reduce the incidence of NEC.To determine whether probiotic supplementation will reduce the incidence of neonatal mortality.To determine whether probiotic supplementation will reduce the incidence of late-onset sepsis.To determine whether probiotic supplementation will reduce the rate and duration of antibiotic use during hospital stay.To determine whether probiotic supplementation will reduce duration of hospital stay.To determine whether probiotic supplementation has an effect on the development and composition of the microbiome.

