### Sample size {14}

The sample size calculation is based on the Swedish average incidence of NEC and mortality in extremely preterm infants, which is comparable for Denmark. During the first two to three postnatal days before the intervention is started, the mortality rate is highest among extremely preterm infants. We will calculate the mortality rate from the start of the third postnatal day, as this is the estimated time the enrolled infants will be exposed to the intervention. Based on pooled incidence rate data from SNQ data from the years of 2019, 2020, and 2021, we considered an 18% base rate of the composite outcome NEC and/or mortality, with an estimated 9% overlap. We estimated a 30% reduction, as this was considered clinically relevant and was also the NEC risk reduction rate seen in the ProPrems trial [6]. After analyzing the relative risk for the power analysis, assuming a significance level of 0.05 and 30% reduction rate with interim analysis based on a Pocock boundary at 1/3, 2/3s, and 100% of the information, the proposed enrollment of 1620 patients will have sufficient power [7] to test our hypotheses. Patient enrollment will continue until this number has been reached. Assuming an 80% consent rate, we expect to enroll 1620 infants in 3 years and 8 months.

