## Discussion

To our knowledge, the PEPS trial is the first sufficiently powered, placebo-controlled RCT evaluating the effect of probiotic supplementation in preventing NEC, total mortality, and other secondary and tertiary endpoints in extremely preterm infants. The results will provide high-quality evidence and likely inform supplementation recommendations in this population. Furthermore, this trial may also add new knowledge on the effect of probiotic supplementation on feeding tolerance and growth, microbiome diversity and development, and body composition in relation to nutritional intake. We believe these results will provide important in-depth knowledge in the context of the results from the main trial.

Despite extensive undertaking of probiotic trials in preterm infants, many challenges have been encountered. Firstly, these trials have often been small in scale and underpowered to effectively evaluate efficacy among extremely preterm infants. Additionally, there has been inconsistency in the selection of outcomes and study populations, rendering studies incomparable. Any combined analyses of these trials have further been limited by their heterogeneity due to considerable variation in investigated probiotic strains and dosages, rendering it difficult to draw clear conclusions [17]. This knowledge gap is especially notable in the case of extremely preterm infants, who are at the highest risk for conditions, such as NEC, sepsis, and mortality. While studies have frequently involved this group of patients, they often fail to specifically examine the effects of probiotics in this population. As a result, there is frequently an inadequate number of patients included and inconclusive groups from the resulting subgroup analysis.

A recent systematic review and meta-analysis of 60 trials with data on 11,156 infants found a 46% lower risk of NEC and 23% lower risk of mortality among very preterm or low birth weight infants following probiotic supplementation [43]. However, these comparisons only provided low or moderate certainty of evidence and the corresponding estimates for extremely preterm or extremely low birth weight infants were not statistically significant for NEC and total mortality. The review further underlined the need for large, high-quality trials, particularly for this population of extremely preterm infants.

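### The two-sided 0.05 rule for claiming an effect covers NEC, total mortality and late-onset sepsis separately, on the same footing as the primary composite

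*Protocol article*

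**What the plan says.** The protocol article ranks its aims. There is one primary aim, the composite of NEC and/or mortality, followed by six secondary and two tertiary aims. In Statistical methods {20a}, one subsection handles primary aim 1 together with secondary aims 1–3. It estimates a relative risk with 95% confidence interval for the composite, "as well as NEC, total mortality, and LOS separately (secondary aims 1–3". It then sets one threshold for the whole subsection: a two-sided p-value "of 0.05 will be considered significant evidence of the effect of the intervention". Nothing in that sentence separates the primary from the secondaries or makes the secondary tests depend on the composite.

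The analysis set is fixed just before: "The primary analysis will be analyzed and reported as ITT". The secondary aims in Objectives {7} are worded as determinations; the mortality aim, for example, reads "To determine whether probiotic supplementation will reduce the incidence of neonatal mortality". The subsections on secondary aims 4–6 and on the tertiary aims state no threshold of their own.

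**The concern.** The rule as written allows significant evidence of an effect to be declared on NEC alone, mortality alone or LOS alone, even when the composite has failed. NEC and death are the two components of the composite, so a split result, with one component significant and the composite not, is a realistic outcome.

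The article says the results may inform national guidelines. A lone secondary p<0.05 would meet the protocol's own standard of evidence, although three such tests together carry more than a 5% chance of a false finding. If the status of these outcomes is settled only after unblinding, the decision will look post hoc.

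**Working it through.** **1. Reproduce the plan's sample size, to confirm that it rests on the composite.** Inputs from Sample size {14}: "we considered an 18% base rate of the composite outcome NEC and/or mortality, with an estimated 9% overlap"; a relative reduction of 30%; two-sided 0.05; Pocock looks at 1/3, 2/3 and full information; "the proposed enrollment of 1620 patients will have sufficient power", with no power figure given. I assume 80%.

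- Treated rate: 0.18 × 0.70 = 0.126; mean rate 0.153.
- n per arm = [1.960·√(2·0.153·0.847) + 0.842·√(0.18·0.82 + 0.126·0.874)]² / 0.054² ≈ 2.031 / 0.002916 ≈ 697, so 1394 in total.
- Pocock inflation for three looks at 80% power: 1394 × 1.166 ≈ 1625, against the stated 1620. Simulated group-sequential power at 1620 is 80.1%.

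The figure reproduces, and it is for the composite only.

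**2. Simple bound for three tests at 0.05 under a global null (no effect on any outcome).** If the three are independent:

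- any significant result, either direction: 1 − 0.95³ = 14.3%
- any significant result favouring the probiotic: 1 − 0.975³ = 7.3%

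**3. Allow for the link between NEC and death.** The article does not give separate rates for NEC and death, nor say whether the 9% overlap is percentage points or a share of the composite. Both readings are used. With the composite held at 18%, death rate = 0.18 − NEC rate + overlap. The correlation is φ = (overlap − NEC × death) / √[NEC(1−NEC) × death(1−death)].

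- Overlap of 9 points, NEC 13.5%, death 13.5%: φ = (0.09 − 0.0182) / 0.1168 = 0.61.
- Overlap of 9% of the composite (0.09 × 18% = 1.62 points), NEC 10%, death 9.62%: φ = (0.0162 − 0.0096) / 0.0885 = 0.07.

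**4. Simulate trials of 810 per arm under the null** (200,000 per row). Each outcome is tested once, at the final analysis, at two-sided 0.05. LOS is assumed to have a 20% rate and to be independent of NEC and death.

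| NEC rate | Overlap | Any of 3 secondaries | Any of 3, favouring probiotic | Secondary significant, composite not | Any of all 4 |
|---|---|---|---|---|---|
| 10% | 1.62 points | 14.2% | 7.2% | 11.0% | 16.1% |
| 10% | 3 points | 14.1% | 7.2% | 10.7% | 15.8% |
| 10% | 5 points | 14.0% | 7.2% | 10.4% | 15.5% |
| 12% | 9 points | 13.3% | 6.8% | 9.4% | 14.4% |
| 13.5% | 9 points | 13.3% | 6.7% | 9.5% | 14.5% |

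In a normal approximation, giving LOS a correlation of 0.2 with both other outcomes moves the first result only slightly: 13.2% instead of 13.3% when the NEC–death correlation is 0.6.

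**The case against.** **The analysis plan may settle this.** A multiplicity scheme for secondary outcomes is commonly left to the SAP or the full protocol, and neither is shown. That stands: the absence of a testing order is not the finding. But the article is not silent. It fixes a claim rule and names the outcomes under it, and a later hierarchy in the SAP would conflict with this published sentence.

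**The aims are already ranked.** A reader might infer that there is no hierarchy at all, or that the trial's main error rate is inflated. The article does not support that. It names one composite primary and sizes the trial on it, and the secondary tests do not change the primary's error rate.

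**The 13–14% is not a false-benefit rate.** A reader might take it as the chance of a positive claim. The aims are to reduce incidence, and about half of those results would point towards harm. The false-benefit figure is about 7%. The larger figure is right for the rule as written, which is two-sided.

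**Aims 4–6.** It is tempting to quote a larger error over all secondary aims. No threshold is stated for those aims, and for beta diversity the text describes a plot and names no test. No figure should be claimed there.

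**Unadjusted secondaries are a common convention.** True, provided they are read as supportive. The 0.05 sentence gives them the same evidential standard as the primary instead.

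**The Discussion's description of the trial.** It calls this the "first sufficiently powered, placebo-controlled RCT evaluating the effect of probiotic supplementation in preventing NEC, total mortality, and other secondary and tertiary endpoints". That concerns power, not error control. It shows how these outcomes are presented but does not prove the point.

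**Gating mortality could mute a harm signal.** This is a fair warning, and it shapes the fix.

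**Conclusion.** The point holds for the composite and secondary aims 1–3. One unconditional 0.05 rule gives NEC, total mortality and LOS the standing of the primary. Under a global null at the final analysis, the chance of at least one significant secondary is about 13–14% in either direction and about 7% for a false benefit. A significant secondary with a non-significant composite occurs in about 9–11% of such trials, roughly twice 5%.

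These figures rest on an 18% composite rate, assumed splits between NEC and death under both readings of the overlap, an assumed independent LOS rate of 20%, and a single test per outcome. They leave out the interim looks, which are a separate matter. The primary conclusion is not invalidated. The published claim rule for three clinically weighty secondaries is too permissive and should be corrected before unblinding.

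**What to change.** In Statistical methods {20a}, state that the significance rule applies to the composite only. For NEC, total mortality and LOS, choose one of two treatments and write it down:

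- **Supportive:** report relative risks with 95% confidence intervals, without a claim of significant evidence; or
- **Adjusted:** apply Holm across the three (smallest p-value against 0.05/3 = 0.0167, the next against 0.05/2 = 0.025, the last against 0.05), stopping at the first failure, and claim benefit only if the composite succeeds.

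State also that safety review of mortality and other harms lies outside this gate, so that a difference in the harmful direction is examined whatever the composite shows. A fixed order among the three would also work statistically, but the article gives no basis for choosing one.

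The cost is a few sentences in the protocol and SAP, with no extra infants or data. The downside is that an isolated secondary p<0.05 after a failed composite can no longer be claimed as significant evidence.

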## Introduction

### Background and rationale {6a}

Despite considerable improvements in preterm infant care in the last decade, approximately 20% of extremely preterm infants, defined as those born before 28 weeks’ gestational age, do not survive past the neonatal period in Sweden [1]. Extremely preterm infants are at a considerably high risk for serious adverse outcomes, including necrotizing enterocolitis (NEC), late-onset sepsis (LOS), and death [2]. Necrotizing enterocolitis, an inflammatory gastrointestinal disease, is regarded as the most severe gastrointestinal-related morbidity in preterm infants and has a high mortality rate [3, 4]. Due to the severity and high incidence of the disease in preterm infants, recent research has focused on preventative measures to combat the development of NEC. One such measure is the supplementation of probiotics, which is thought to improve gastrointestinal tolerance and colonization of beneficial bacteria in these infants, ultimately helping their microbiota resemble that of a healthy infant. To date, preemptive provision of probiotics for NEC prevention has gained immense clinical and research interest worldwide.

The Probiotics in Extreme Prematurity in Scandinavia trial (PEPS trial) is comprised of two parts. The first part is a multicenter trial which aims to investigate the effect of probiotic vs. placebo supplementation on the incidence of NEC and death. This cohort will hereafter be referred to as the “complete cohort.” The second part aims to assess the effect of probiotic supplementation on feeding tolerance, postnatal growth, and body composition. This analysis will solely be conducted on a cohort of infants at Karolinska University Hospital in Stockholm, Sweden, due to limited availability of feeding and growth data at other sites. This population will hereafter be referred to as the “sub-cohort.”

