### Antibiotic treatment

Once NEC or LOS is suspected or confirmed, immediate antibiotic treatment is routinely started. According to the Swedish Neonatal Quality Register (SNQ), the mean duration of antibiotic treatment for extremely preterm infants is around 25 days [1]. Previous research has found that infants receiving antibiotic treatment during the first week of life have an altered gut microbiome with lower bacterial diversity, the extent of which was recently explored in a study of 32 preterm infants [32, 35]. Consequently, antibiotic-induced microbiome alterations have been linked to gastrointestinal diseases in preterm infants and developmental growth changes in term infants, including higher body mass indices (BMI) [36, 37]. Hence, antibiotics used for the treatment of NEC and LOS may also be associated with short- and long-term health consequences in preterm infants.

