***Secondary outcome variables***			
Late-onset sepsis	Incidence rate	Mean/Median	During study intervention (until 34 weeks of gestational age)
Verified late-onset sepsis^b^	Incidence rate	Mean/Median	During study intervention (until 34 weeks of gestational age)
Late-onset sepsis Culture-proven	Type of pathogen	Sum	During study intervention (until 34 weeks of gestational age)
Late-onset sepsis date	Date of onset	Sum	During study intervention (until 34 weeks of gestational age)
Late-onset sepsis Peripheral line at onset	Yes/No	Mean/Median	During study intervention (until 34 weeks of gestational age)
Late-onset sepsis Central line at onset	Yes/No	Mean/Median	During study intervention (until 34 weeks of gestational age)
Use of antibiotics	Rate of prescription (number) Duration of treatment (days)	Mean/Median	During study intervention and until 40 weeks of gestational age
Length of stay	Number of days	Mean/Median	Length of stay at the neonatal intensive care unit Length of stay at homecare
Effect on microbiome	Fecal samples		1. Directly after inclusion ± 2 days 2. 14 ± 2 days gestational age 3. 34 weeks ± 2 days gestational age 4. 12 months corrected age ± 2 weeks
***Serious adverse event*** (Necrotizing enterocolitis, death and late-onset sepsis included)			
Bronchopulmonary dysplasia	Yes/No	Mean/Median	During study intervention (until 34 weeks of gestational age)
Respiratory distress syndrome	Yes/No	Mean/Median	From birth and during study intervention (until 34 weeks of gestational age)
Patent ductus arteriosus (PDA)	Yes/No	Mean/Median	From birth and during study intervention (until 34 weeks of gestational age)
Pulmonary hypertension	Yes/No	Mean/Median	During study intervention (until 34 weeks of gestational age)
Intraventricular hemorrhage	Yes/No	Mean/Median	During study intervention (until 34 weeks of gestational age)
Hydrocephalus	Yes/No	Mean/Median	During study intervention (until 34 weeks of gestational age)
Retinopathy of prematurity	Yes/No	Mean/Median	During study intervention (until 34 weeks of gestational age)

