#### Data collection and assessment for sub-cohort

Data on postnatal growth (Table 3) during the intervention period will be registered as per clinical routine in the nutritional calculation software, Nutrium (nutrium.se). All growth data from the intervention period will be retrieved from Nutrium. Growth data during long-term follow-up will be collected from SNQ and/or medical records (sub-cohort).

**Table 3 Tab3:** Description of outcomes with analysis metric, aggregation method, and time points in sub-cohort

Outcome variables sub cohort			
*Outcome variables - feeding tolerance*	*Analysis metrics*	*Method of aggregation*	*Time point*
Enteral nutrition	Number of days until full enteral feeds	Mean/Median	During study intervention (until 34 weeks of gestational age)
Parental nutrition	Number of days with parental nutrition	Mean/Median	During study intervention (until 34 weeks of gestational age)
Interruptions of enteral nutrition	Number of enteral nutrition interruptions >8 h	Mean/Median	During study intervention (until 34 weeks of gestational age)
Enteral nutrition decreased due to clinical instability	Number of EN decrease >50%	Mean/Median	During study intervention (until 34 weeks of gestational age)
Use of breastmilk fortifiers	Number of days until breastmilk fortifiers is induced	Mean/Median	During study intervention (until 34 weeks of gestational age)
Feeding tube requirement	Number of days requiring a feeding tube	Mean/Median	During study intervention and until 40 weeks of gestational age
Macronutrient intake	Amount of macronutrients given (kcal/kg/day)	Mean/Median	During study intervention (until 34 weeks of gestational age)
Micronutrient intake	Amount of micronutrients given (μg or mg/kg/day)	Mean/Median	During study intervention (until 34 weeks of gestational age)

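### Length of stay and antibiotic days are modelled with no rule for infants who die, so a mortality difference between arms can distort both comparisons

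*Protocol article*

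**What the plan says.** The Secondary aims section makes fewer days the benefit for both outcomes: "To determine whether probiotic supplementation will reduce the rate and duration of antibiotic use during hospital stay" and "To determine whether probiotic supplementation will reduce duration of hospital stay".

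Table 1 measures antibiotics as a number of prescriptions and as days of treatment, over a window that runs to 40 weeks of gestational age. It measures stay as a number of days, split into "Length of stay at the neonatal intensive care unit Length of stay at homecare".

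The model is set in Statistical methods {20a}, under secondary aims 4 and 5: the rate and duration of antibiotic use and "duration of hospital stay (secondary aim 5) will be analyzed using standardized logistic regression and linear regression model". The opening of {20a} says that data are analysed both by intention to treat and per protocol.

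Table 1, {20a}, {20b} and {20c} do not say how an infant who dies before discharge, or before 40 weeks, enters these analyses. Section {20c} deals with non-adherence and with gaps in registry data; death is neither. In the sub-cohort, Table 3 adds "Number of days until full enteral feeds", and the tertiary aims are given the same two model types.

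**The concern.** Stay and antibiotic days stop accruing at death, and death is one of the outcomes the product is meant to reduce. The named regressions can be run in two ways, and neither gives a sound effect on stay or on antibiotic use.

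- **All randomised infants, observed days.** An infant who dies in the third week contributes a short stay and few antibiotic days. On the scale that the aims define, that is a good result. A difference in mortality then moves the mean difference even when the product does nothing to stay or antibiotic use in survivors.
- **Survivors only.** The groups compared are selected by an event that follows randomisation and that the treatment may change.

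At stake are two secondary conclusions. A life-saving product could appear to prolong stay and antibiotic use. A harmful one could appear to shorten them.

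**Working it through.** The article states no expected stay or antibiotic effect and no sample size for these aims, so there is no figure of the plan's own to reproduce. Its 1620 infants relate to the primary composite.

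**Inputs from the article**
- Composite of NEC and/or death: 18% in controls, deaths counted from the third day (Sample size {14}). Mortality alone is not given. It can be at most 18%, and would reach that only if every composite event included a death.
- Relative reduction: 30%, stated for the composite ({14}) and applied here to death as an assumption.
- Allocation 1:1 ({8}), so 810 per arm.

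**Assumed inputs**
- Control mortality of 8% to 12%.
- Stay of 90 to 100 days in survivors and 20 to 25 days in infants who die.
- Antibiotic days: 25 in survivors, 12 in infants who die.
- No effect of the product in survivors.

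**Formula.** Mean per arm = (1 − m) × survivor days + m × days in infants who die, where m is mortality. With survivors identical in both arms, the difference (probiotic minus placebo) = (m control − m probiotic) × (survivor days − days in infants who die).

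**Stay, higher case** (12% v 8.4%; 100 and 20 days)
- Placebo: 0.88 × 100 + 0.12 × 20 = 90.4
- Probiotic: 0.916 × 100 + 0.084 × 20 = 93.3
- Difference: 0.036 × 80 = 2.9 days longer on probiotic

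**Stay, lower case** (8% v 5.6%; 90 and 25 days)
- Placebo: 0.92 × 90 + 0.08 × 25 = 84.8
- Probiotic: 0.944 × 90 + 0.056 × 25 = 86.4
- Difference: 0.024 × 65 = 1.6 days longer on probiotic

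**Antibiotic days** (gap 25 − 12 = 13): 0.024 × 13 = 0.3 and 0.036 × 13 = 0.5 more days on probiotic.

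**Reversed direction.** If mortality rose by 30%, from 12% to 15.6%, the probiotic mean would be 0.844 × 100 + 0.156 × 20 = 87.5. That is 2.9 days shorter than placebo: an apparent benefit produced by extra deaths.

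**Wider range for stay.** Control mortality of 6% to 18% and a gap of 50 to 90 days give 0.018 × 50 = 0.9 to 0.054 × 90 = 4.9 days. The upper end is a ceiling, because it needs 18% mortality.

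**Chance of a significant artefact.** Take 12% v 8.4% and a gap of 70 days: 0.036 × 70 = 2.52 days. The standard error is SD × √(2/810), which is 1.49 for an assumed SD of 30 days and 1.99 for 40. The chance of p < 0.05 is then about 39% and 24%, against a nominal 5%. Smaller SDs are hard to defend: mixing deaths with survivors alone gives √(0.12 × 0.88) × 70 = 23 days in the control arm.

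**The case against.** **Death may be handled in the SAP, and the article never says that it scores as a short stay.** This is right as far as it goes. The sentence placing every randomised infant in the analysis stands under the primary aim and secondary aims 1–3; for aims 4 and 5 there is only the general intention-to-treat statement. That early deaths enter as short stays is therefore an inference about one way of running the model. But the article does name the model, and the other obvious way, survivors only, does not rescue it.

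**Mortality may be modest.** A reader might take the statement that "approximately 20% of extremely preterm infants" do not survive the neonatal period as the trial's mortality. It is not. That figure counts from birth, whereas {14} puts the highest mortality in the first two to three days and counts only later deaths, and infants with a low chance of survival are excluded. The 30% reduction is also borrowed from the composite, and the background section reports no significant mortality effect in the ProPrems trial. A smaller mortality difference shrinks the artefact in proportion.

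**Survivors may benefit.** A reader might infer that the trial will report a longer stay if probiotics save lives. That holds only if survivors gain little. In the higher case, a stay 2.88 / 0.916 = 3.1 days shorter in probiotic survivors would cancel the artefact. Mortality is also reported as its own secondary outcome, so a careful reader could see part of the explanation.

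**Logistic regression is not shown to be unsuitable.** The article lists two model types without assigning them to outcomes, and logistic regression for any use with linear regression for days is a natural reading. That "the mean duration of antibiotic treatment for extremely preterm infants is around 25 days" does not show that nearly every infant is exposed.

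**Days to full feeds is a different problem.** An infant who dies before full feeds has no value for this outcome, rather than a favourable short one.

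**Conclusion.** The point stands for secondary aims 4 and 5. The article commits to regressions on days, counts fewer days as success, and says nothing about infants who die, while death is expected and may differ by arm. The artefact is the mortality difference times the survivor-minus-death gap.

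The sizes found, 1.6 to 2.9 days of stay (about 2% to 3% of the mean) and 0.3 to 0.5 antibiotic days, rest on assumed mortality, assumed gaps, a 30% reduction applied to death, and no effect in survivors. They show scale and direction and are not forecasts. The stay artefact is small beside the mean, but with 810 infants per arm it can reach nominal significance.

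In the sub-cohort, days to full feeds is undefined after an earlier death and needs its own rule. The primary outcome is unaffected. The change should be made before unblinding.

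**What to change.** - **Aim 5.** Replace the linear model with time to discharge alive, with death as a competing event (cumulative incidence by arm and a subdistribution model). Alternatively, use days alive and out of hospital to a fixed day, with deaths scored zero. State whether discharge means leaving the NICU or the end of homecare, since Table 1 lists both.
- **Aim 4.** Use a measure that includes deaths, such as antibiotic-free days alive to 40 weeks with deaths scored zero, and read it beside mortality. Antibiotic days per day alive would not be an equal substitute: it turns the question from duration to intensity, and it conditions on time after randomisation that death itself cuts short.
- **Sub-cohort.** Analyse days to full enteral feeds as time to event with death competing.
- **Survivors.** Give survivor-only means as description.

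The cost is protocol or SAP wording and modest extra analysis. The effect measures are less familiar than a mean difference, and those that score death as zero combine mortality with days. Check first that discharge and antibiotic dates will be available. The article reports these outcomes as counts of days, its listed eCRF items include neither date, and the full data list is in an additional file that is not shown.
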